# 4.3 Description of research methodology

# 4.3.1 Recruitment

The study will take the First Affiliated Hospital of Xi’an Jiaotong University as the principle research center, allying with 11 Sub-Centers, Affiliated Hospital of Shaanxi University of Chinese Medicine, First Affiliated Hospital of Henan University of Chinese Medicine, First Affiliated Hospital of Henan University of Science and Technology, First Hospital of Hunan University of Chinese Medicine, General Hospital of Ningxia Medical University, Henan Provincial People's Hospital, Hunan Provincial People's Hospital, Second Hospital of Shanxi Medical University, Shanxi Provincial Hospital of Traditional Chinese Medicine, Shuguang Hospital Affiliated to Shanghai University of Traditional Chinese Medicine, Tianjin Third Central Hospital. The study will recruit the patients scheduled for laparoscopic non-gastrointestinal surgery under general anesthesia in 12 hospitals above between September 2019 and February 2021.

### Prescreening and rescreening

All investigators will be trained and will follow the trial protocol. Researchers will assess whether the scheduled patient meets the criteria one day before the surgery. Informed consent will be signed if the patient meets the eligibility, and then make an evaluation of self-rating anxiety scale (SAS). Patients’ eligibility for recruitment will be reassessed after extubation. The patients given conversion to open laparotomy, occurring skin allergy, breakage, infection or itching of test points, refusing to participate or unplanned admission to ICU will be excluded from the trial. If they are eligible, randomization will be performed. Using Crabyter scientific research system (Xinyu Information Technology Co., Ltd) for block randomization, the enrolled patients will be randomly divided into Sham and TEAS groups in a 1:1 ratio (with a block size of 4) to verify the reliability of TEAS in PONV prevention. The enrolled patients will be assessed by Richmond Agitation-Sedation Scale (RASS).

### 4.3.3 Pharmacologic and non-pharmacologic intervention

Attending anesthesiologists administrated PONV prophylaxis in operation room. Dexamethasone 5 mg IV and the second-generation 5-hydroxytryptamine 3 (5-HT3) receptor antagonists palonosetron 0.075 mg are administrated before anesthesia induction as the first choice. When palonosetron was not available at some hospitals, patients received dexamethasone 5 mg (before induction) combined with tropisetron 2 mg (at the end of surgery) instead. According to the criteria of WHO acupuncture points, Neiguan (P6) and Zusanli (ST36) will be selected in this study. As shown in the Supplementary Figure 1, these acupoints are far from the operation site. P6 is located at 2 inches above palm wrist transverse striation, between the palm long tendon and the temporal flexor tendon. ST36 is located at 3 inches below EX-LE5 (the lateral pit of the patella and patellar ligament), and one transverse finger outward lateral tibia. The electrode slice has a single conductive emboss and two connecting wires, thereby enabling non-invasive, accurate and convenient stimulation. The TEAS treatments will be scheduled to conduct twice in total, respectively during anesthesia recovery in PACU (to be awake and calm, RASS = 0) and in the next-morning of surgical ward for 30 minutes.

**TEAS group:** When patients recover from anesthesia status to a degree of the Steward recovery score ≥ 4 in PACU and the endotracheal tubes are withdrawn, the first TEAS treatment will be performed. The bilateral P6 and ST36 will be pressed to achieve a tingling sensation called “de qi”, and electrode slices will be stuck and fixed on those acupoints. Interveners will connect electrode slices to electrical stimulator and select the distant-dense wave with the frequency of 2/10Hz. After adjusting the intensity to the patient’s maximum tolerance, he/she will be treated for 30 minutes. Another TEAS treatment will be performed between 9 am and 12 am in the ward on the first postoperative day; meanwhile, patients will receive routine health education including illness, diet, exercise and psychological considerations.

**Sham group:** Electrode slices will be stuck at the same acupoints as in TEAS group. The interveners will connect electrode slices to stimulator through the internally broken wires and set the same treatment procedure with key sound. The treatment will last for 30 minutes without adjusting to the patient’s maximum tolerance intensity. To protect the rights of patients, the interveners will receive the same health education as it in TEAS group in the morning of the first postoperative day.

## 4.4 Description of measures taken to reduce and avoid bias

### 4.4.1 Randomization

Crabyter scientific research system (Xinyu Information Technology Co., Ltd) will be used for block randomization, with four patients comprising each block. Each center will compete into block to enroll subjects. A block group will be randomly allocated into TEAS group or Sham group at a ratio of 1: 1, with four patients regarded as one block. This random method ensures that the number of patients in two groups will be essentially equal with highly efficient enrollment.

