### 4.4.2 Blinding method

Patients will be blinded when being allocated and cannot detect any difference in the entire procedures. This procedure will be the same in both groups, except that the connecting wires inside the stimulators will be broken in the Sham group. Therapeutic evaluators will be blinded in the process of allocation, screening, intervention treatment and statistical analysis. To prevent the leakage of allocation, evaluator will not play any other roles in the study, and we will apply spatial and temporal isolation for interventions and evaluations. Interventions will be conducted in PACU and ward, whereas evaluations will be performed only in the ward. Interventions and evaluations will be performed during different periods in ward. Interventions will be conducted once a day between 9 am and 12 am in the ward, whereas evaluations will be performed after 12 am. When the patient is randomized, an evaluator will complete the entire process of evaluation in a blinded intervention progress. A random administrator will be selected from principle investigator research center. This administrator will not play any other roles in the study. The external statistical experts will be blinded to allocation, and the statistical calculations will be independently conducted.

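### The fixed, disclosed block size of four leaves a small, avoidable prediction risk at the post-extubation eligibility recheck; shared blocks keep that risk small but give no within-centre balance.

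*Protocol*

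**What the plan says.** Sections 4.1, 4.3 (Prescreening and rescreening) and 4.4.1 of the protocol all give the same block size. Section 4.4.1 states that the research system "will be used for block randomization, with four patients comprising each block". The size is therefore open to site staff, who work from this document: "All investigators will be trained and will follow the trial protocol".

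Blocks are common to all sites: "Each center will compete into block to enroll subjects". Section 4.3.1 recruits patients "under general anesthesia in 12 hospitals above between September 2019 and February 2021". No stratification factor is named. The only balance claimed concerns the arm totals: "This random method ensures that the number of patients in two groups will be essentially equal with highly efficient enrollment".

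Under Prescreening and rescreening, "eligibility for recruitment will be reassessed after extubation". The listed grounds for exclusion at that step include itching at the test points and refusal to take part. Eligible patients are then randomized.

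Section 4.4.2 lists patients, evaluators and external statisticians as blinded. Interveners are not on that list. Section 4.3.3 has them raise the current to tolerance in the TEAS arm only, and use internally broken wires without adjustment in the Sham arm. On separation of duties, section 4.4.2 says that the "evaluator will not play any other roles in the study", and it places the same bar on the random administrator. It places none on interveners.

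**The concern.** Someone who knows recent allocations and the block size can form a view of the next one. If that person also judges eligibility after extubation, a discretionary ground could be used to keep a patient out when the expected arm is unwelcome. Such selection would act before randomization, so neither the blinding of evaluators nor an intention-to-treat analysis would remove it.

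Blocks filled by all centres together also do not control the arm split inside any one hospital. Section 4.3.3 makes the choice of 5-HT3 antagonist depend on what each hospital has available, so a factor that may affect the primary outcome is tied to centre.

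**Working it through.** The protocol gives no figure for predictability or for balance within centres, so there is none of its own to reproduce.

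**Inputs from the protocol.** Block size 4, ratio 1:1, 12 centres, common blocks. Total 1634 (section 9) or 1655 (Summary), so 1634/12 = 136 or 1655/12 = 138 patients per centre if centres are equal.

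**Assumed, because the protocol is silent.** Centre shares: equal, or one centre with 40%. Arrival: random, or in runs of 2 or 3 patients from one centre. Each site sees only its own allocations.

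**1. Upper limit: one site sees the whole block.** The best guess is right with probability 1/2, 2/3, 2/3 and 1 at positions 1 to 4. The mean is (0.500 + 0.667 + 0.667 + 1)/4 = 70.8%. Position 4 is always certain and position 3 is certain with probability 1/3, so (1 + 1/3)/4 = 33.3% of allocations are certain.

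**2. Shared blocks, random arrival.** The rule is to guess the opposite of the site's own last allocation. Two patients in the same block of four are in different arms with probability 2/3, which is 1/2 + 1/6. For a centre with share s:

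P(same block) = s(3/4) + s(1−s)(2/4) + s(1−s)²(1/4)

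P(correct) = 0.5 + P(same block)/6

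- s = 1/12: 0.0625 + 0.0382 + 0.0175 = 0.118, so 52.0%
- s = 0.20: 0.150 + 0.080 + 0.032 = 0.262, so 54.4%
- s = 0.40: 0.300 + 0.120 + 0.036 = 0.456, so 57.6%

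**3. Shared blocks, clustered arrival (simulation).** With runs of 2 or 3 the same rule is right about 59% of the time over all centres, and about 60% at a centre with a 40% share. Blocks filled wholly by one centre make up 0.06% (equal shares) to 2.5% (one centre at 40%) with random arrival, and 8% to 19% with runs.

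**4. Effect of varying the size, blocks still shared.** With sizes 4, 6 and 8 drawn at random, the rule falls from about 58–59% to about 56% under clustered arrivals. With equal centres and random arrival it stays at about 52%.

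**5. Effect of stratifying by centre.** In a block of b within one centre, the b−1 adjacent pairs differ with probability b/[2(b−1)], and the step into the next block differs with probability 1/2. The same rule is then right (b/2 + 1/2) times per b patients.

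- Fixed 4: 2.5/4 = 62.5%
- Sizes 4, 6, 8: (2.5 + 3.5 + 4.5)/18 = 58.3%

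A best guess from the full local history does better: 70.8% with fixed fours (step 1), and about 68%, with about 2% of allocations certain, for sizes 4, 6 and 8 (simulation).

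**6. Balance within centres under shared blocks.** Simulation with 12 equal centres of about 138 gives a mean absolute arm difference of 9.0. Simple randomization gives √(2 × 137.9/π) = 9.4. Over the whole trial the difference stays at 2 or less. A split of 60:40 or worse, from Binomial(n, 0.5), has probability 2.0% at n = 136 (82 or more in one arm). At assumed centre sizes of 40 and 80 it is 26.8% and 9.3%.

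**The case against.** The strongest reply is that sharing blocks across 12 centres is itself a form of concealment: each site sees only fragments of a block. That stands. A reader might infer from the block size that a third of allocations are certain and 71% can be guessed. The protocol does not support this, because it has centres filling common blocks and does not say that staff see other centres' allocations. It does not rule that out either.

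A reader might also infer that interveners do the recheck. The protocol does not say so; it only fails to bar it. The stated order is eligibility first, then randomization, and Table 1 agrees. Of the discretionary grounds, refusal belongs to the blinded patient. That interveners know the arm is likewise inferred from the procedures, not stated.

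On balance, a reader might take centre imbalance as a source of bias. It is not: the imbalance arises by chance, the unstratified comparison in section 9 remains valid, and the protocol promises only near-equal totals. Leaving out stratification is a choice, not an error. Stratifying would also give up part of the concealment that sharing provides.

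What the reply does not answer is why the size should be both fixed and disclosed, when neither serves a purpose at the sites.

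**Conclusion.** The point holds as a low-cost improvement. It is not a threat to the trial's validity as designed. A fixed and disclosed block of four gives a site a guess that is right about 52% to 60% of the time, against 50% with no information. This range rests on the assumed centre shares and arrival patterns, on sites seeing only their own allocations, and on the simple last-allocation rule; a guess that used the full local history could do somewhat better. If staff can see all allocations in a block, the 71% and 33% apply instead.

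The lack of balance within centres is real, with a mean difference of about 9 patients in roughly 137, almost as under simple randomization. Its consequence is limited to some loss of precision and to weaker readings by centre or antiemetic regimen.

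**What to change.** In section 4.4.1, state that the central system uses randomly varying block sizes. Remove the size from sections 4.1, 4.3 and 4.4.1 and hold the sizes in a restricted randomization file. Require the system to record the post-extubation eligibility decision before it releases the allocation.

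The cost is system configuration and a short rewrite, with no added patients or staff and no change to the sample size. Competitive enrolment can continue. The downside is that arm totals may differ by a few patients: an incomplete last block can leave a gap of half its size, so up to 4 with a block of 8, against 2 now.

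Stratifying by centre is optional. It restores balance within hospitals, but it makes the local sequence easier to predict than shared blocks of the same sizes (58.3% for stratified 4, 6 and 8 under the last-allocation rule, against about 52–56% when those sizes are shared in the equal-centre patterns above). If it is adopted, use it only with varied, undisclosed sizes and state the trade-off.

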### 4.4.2 Blinding method

Patients will be blinded when being allocated and cannot detect any difference in the entire procedures. This procedure will be the same in both groups, except that the connecting wires inside the stimulators will be broken in the Sham group. Therapeutic evaluators will be blinded in the process of allocation, screening, intervention treatment and statistical analysis. To prevent the leakage of allocation, evaluator will not play any other roles in the study, and we will apply spatial and temporal isolation for interventions and evaluations. Interventions will be conducted in PACU and ward, whereas evaluations will be performed only in the ward. Interventions and evaluations will be performed during different periods in ward. Interventions will be conducted once a day between 9 am and 12 am in the ward, whereas evaluations will be performed after 12 am. When the patient is randomized, an evaluator will complete the entire process of evaluation in a blinded intervention progress. A random administrator will be selected from principle investigator research center. This administrator will not play any other roles in the study. The external statistical experts will be blinded to allocation, and the statistical calculations will be independently conducted.

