### 4.4.3 Follow-up

Electronic patient self-reported scale (Jiangsu Rehn Medtech Technology Co., Ltd) will be applied to evaluate and record the occurrence of PONV in real time, including the time to each PONV and corresponding VAS score. The VAS is a simple-to-use measure to evaluate intensity of PONV. It’s a 10-point numerical rating scale with 0 = “no nausea or vomiting” and 10 = “worst nausea imaginable and vomiting”. The cut points on the PONV VAS have been recommended: mild PONV ( 4), which has little impact on daily activities and does not affect sleep; severe PONV ( 7), which results in inability to sleep and seriously hinders daily life; moderate PONV, whose clinical influence intervenes between the two above. When PONV happens at any time, patients or their caregivers spontaneously assess the severity of PONV with VAS and then send it to the central server through the electronic scale. The evaluator port harvests PONV information immediately so that it can be managed timely. To ensure a blinded fashion, both groups will be evaluated by direct questioning in the ward after 12 am at the 1st and 2nd postoperative day in ward. Persistent nausea was defined as continuous nausea lasting over 5 min. If the patients are discharged on the second day postoperative, they will be assessed by telephone. The postoperative 30-day information about delayed curative efficacy, complications and adverse events will be obtained through telephone follow-ups and electronic medical record system.

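### The claim that patients cannot tell the arms apart conflicts with the protocol's own account of TEAS and Sham, so patient blinding is at serious risk for an outcome that nausea alone can meet

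*Protocol*

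**What the plan says.** Section 4.4.2 (Blinding method) makes two statements about the patient. The first is absolute: "Patients will be blinded when being allocated and cannot detect any difference in the entire procedures". The second limits the difference between arms to one item: "This procedure will be the same in both groups, except that the connecting wires inside the stimulators will be broken in the Sham group".

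Section 4.3.3 describes what is done in each arm.

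- **TEAS:** "The bilateral P6 and ST36 will be pressed to achieve a tingling sensation called" de qi. Then: "After adjusting the intensity to the patient’s maximum tolerance, he/she will be treated for 30 minutes". The first session takes place in the PACU, with the patient extubated, awake and calm (RASS 0). A second follows on the ward the next morning.
- **Sham:** electrodes go on the same acupoints. The interveners "connect electrode slices to stimulator through the internally broken wires and set the same treatment procedure with key sound". The session also lasts 30 minutes, but the text says that the intensity is not adjusted to the patient's tolerance.

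Section 4.2.2 defines the primary outcome as at least one episode of nausea, retching or vomiting within 24 h. Section 4.4.3 gives two sources for it. One is an electronic self-report, in which "patients or their caregivers spontaneously assess the severity of PONV with VAS". The other is direct questioning on the ward on postoperative days 1 and 2.

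The Summary and Sections 2 and 4.1 call the trial evaluator-blinded. They do not call it patient-blinded or double-blind.

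**The concern.** Section 4.4.2 claims a property that the procedures in Section 4.3.3 do not support. A current set to the limit of tolerance is meant to be felt, and an open circuit delivers nothing. Setting it also needs feedback from the patient, so the contact between intervener and patient differs too, and Section 4.4.2 does not list that difference.

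This matters because of the outcome. Nausea is subjective, only the patient can perceive it, and a single episode is enough. If patients who feel a strong current report mild nausea less readily than patients who feel nothing, the resulting difference in PONV incidence cannot be separated from a treatment effect. The planned effect is only 7 percentage points, so a modest reporting difference would count.

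**Working it through.** **1. The sections side by side**

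| Feature | TEAS (4.3.3) | Sham (4.3.3) | Admitted as a difference in 4.4.2? |
| --- | --- | --- | --- |
| Electrode sites, 30-minute duration | Same | Same | Not a difference |
| Wires and current | Intact, current flows | Internally broken, no current | Yes |
| Adjustment to tolerance | Done | Stated as not done | No |
| Pressing to a tingling sensation | Described | Not mentioned | No |

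The second row alone undercuts the statement that no difference can be detected, since an awake patient can feel current at maximum tolerance. Section 8 agrees: it lists discomfort from the electrical stimulation among the possible adverse reactions. The third row contradicts the statement that the wires are the only difference.

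**2. What the safeguards reach**

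Section 4.4.2 provides a separate evaluator and keeps interventions and evaluations apart in place and time. These measures stop the evaluator from learning the allocation. They do not affect what the patient felt. Ward evaluation comes after the morning intervention window, so by the first direct questioning a TEAS patient would normally have had both sessions. The evaluator then records what the patient says.

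**3. Reproducing the plan's own figure**

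Inputs from Section 9: 40% in Sham, a reduction of 7 points to 33%, significance 0.05, power 80%. Section 9 does not say whether the test is one- or two-sided; two-sided reproduces its result. Pooled two-proportion formula, no continuity correction, mean rate 0.365:

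n = [1.960 × √(2 × 0.365 × 0.635) + 0.842 × √(0.40 × 0.60 + 0.33 × 0.67)]² / 0.07²
= [1.960 × 0.6808 + 0.842 × 0.6790]² / 0.0049
≈ 3.633 / 0.0049 ≈ 741.3, rounded up to **742 per group**, as stated.

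The sample size arithmetic is not in question.

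**4. Illustration of a reporting-only difference**

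Assumptions, not in the documents: TEAS has no true effect, the Sham rate is 40%, and reporting alone lowers the TEAS rate by b. With n = 742 per arm, p₁ = 0.40, p₂ = 0.40 − b and p̄ their mean:

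- SE₀ = √(2p̄(1 − p̄)/n), SE₁ = √((p₁(1 − p₁) + p₂(1 − p₂))/n)
- P(significant) = Φ((b − 1.96 SE₀)/SE₁) + Φ((−b − 1.96 SE₀)/SE₁)

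For b = 0.02, SE₀ and SE₁ are both about 0.0253. The first term is Φ((0.02 − 0.0496)/0.0253) = Φ(−1.17) ≈ 0.121, the second is about 0.003, and the sum is 0.124.

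| Assumed b | 742 per arm | 817 per arm (1634/2) |
| --- | --- | --- |
| 0 | 5.0% | 5.0% |
| 1 point | 6.8% | 7.0% |
| 2 points | 12.4% | 13.2% |
| 3 points | 22.1% | 23.8% |
| 5 points | 51.2% | 55.1% |

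At 7 points the calculation returns 80%, but that only restates the design power with the planned effect relabelled as bias. It says nothing about how likely such a bias is.

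**The case against.** A reader might infer that the trial is in effect unblinded for patients. The documents do not support that. Groups are parallel, so no patient can compare the two experiences. Sham shares the acupoints, electrodes, programme, key sound and duration. Patients are not told their arm. Whether a Sham patient infers it depends on what patients were told to expect, and the consent pages are not available. This objection stands: the text establishes a serious risk, not a failure.

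A reader might also infer that pressing is omitted in Sham. Section 4.3.3 is silent on this, and Section 4.4.2 says that the procedure is otherwise the same. The missing adjustment is stated outright; missing pressing is not.

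Third, the design label is already modest. The overclaim sits in Section 4.4.2, not in the description of the trial as a whole. That limits the correction needed but does not remove the contradiction.

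Fourth, the size of any reporting difference is unknown, and no passage supports a particular value. That stands, so the table is an illustration and not an estimate.

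Fifth, it would be too strong to say that blinding will never be checked. Neither Table 1 in Section 4.5 nor the list of forms in Section 7 shows a check, but that list is open-ended.

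It can also be said that direct questioning by a blinded evaluator is a second source for the outcome. It is, but it still depends on the patient's account and does not remove reporting bias.

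**Conclusion.** The point holds as an internal contradiction with a consequence for interpretation. Section 4.4.2 says that patients cannot detect a difference and that only the wires differ. Section 4.3.3 describes a current at maximum tolerance in one arm against no current in the other, and an intensity adjustment in one arm only. Patient blinding is at serious risk, and the primary outcome can be met by a symptom that only the patient can perceive. Evaluator blinding does not protect against that.

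The size is conditional. With a 40% rate, no true effect and 742 per arm, assumed reporting-only differences of 2, 3 or 5 points raise the chance of a significant result from 5% to about 12%, 22% or 51%.

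The conclusion does not rest on patients having been unblinded, which the documents cannot show. Nor is it a matter to leave to a statistical analysis plan: no analysis can change how Sham is delivered or make the blinding statement accurate.

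**What to change.** 1. **Correct the claim.** Withdraw the statement that patients cannot detect any difference and reconcile Section 4.4.2 with Section 4.3.3. Keep the evaluator-blinded label and describe patient blinding as uncertain. Cost: wording only, and a weaker but accurate blinding claim.

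2. **Make the wires the only procedural difference.** State that Sham receives the same point pressing and a mock intensity adjustment, as Section 4.4.2 implies. This equalises the contact with the intervener; it does not make the sensation the same. Cost: brief retraining of interveners at the 12 hospitals.

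3. **Measure patient blinding.** Ask each patient to guess the allocation and report a blinding index by arm. Preferably ask soon after the first session. A guess taken on postoperative day 2 would be mixed with outcome, because patients without PONV may guess TEAS since they did well. Keep the answer from the evaluator. Cost: one question; asking early may itself draw attention to allocation.

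4. **Optional supportive analysis.** If vomiting and retching are recorded separately from nausea, report them as a less subjective companion to the primary outcome. The sponsor should confirm this first, because the severity scale in Section 4.4.3 scores nausea and vomiting together. Cost: one analysis, with fewer events and so less precision.
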